## Abstract

**Background:**

Home visiting programs comprising intensive and sustained visits by professionals (usually nurses) over the first two years of life show promise in promoting child health and family functioning, and ameliorating disadvantage. Australian evidence of the effectiveness of sustained nurse home visiting in early childhood is limited. This paper describes the method and cohort characteristics of the first Australian study of sustained home visiting commencing antenatally and continuing to child-age two years for at-risk mothers in a disadvantaged community (the Miller Early Childhood Sustained Home-visiting trial).

**Methods and design:**

Mothers reporting risks for poorer parenting outcomes residing in an area of socioeconomic disadvantage were recruited between February 2003 and March 2005. Mothers randomised to the intervention group received a standardised program of nurse home visiting. Interviews and observations covering child, maternal, family and environmental issues were undertaken with mothers antenatally and at 1, 12 and 24 months postpartum. Standardised tests of child development and maternal-child interaction were undertaken at 18 and 30 months postpartum. Information from hospital and community heath records was also obtained.

**Discussion:**

A total of 338 women were identified and invited to participate, and 208 were recruited to the study. Rates of active follow-up were 86% at 12 months, 74% at 24 months and 63% at 30 months postpartum. Participation in particular data points ranged from 66% at 1 month to 51% at 24 months postpartum. Rates of active follow-up and data point participation were not significantly different for the intervention or comparison group at any data point. Mothers who presented for antenatal care prior to 20 weeks pregnant, those with household income from full-time employment and those who reported being abused themselves as a child were more likely to be retained in the study. The Miller Early Childhood Sustained Home-visiting trial will provide Australian evidence of the effectiveness of sustained nurse home visiting for children at risk of poorer health and developmental outcomes.

**Trial registration:**

ACTRN12608000473369

## Background

Health is not equally distributed in our community. Children born in areas of disadvantage do not have the same opportunity for good health as those living in more advantaged areas [1,2]. In Australia and internationally there is increased interest in developing interventions that will reduce health inequalities and recognition that early childhood interventions offer the greatest potential for long term change [3].

Home visiting programs comprising intensive and sustained visits by professionals (usually nurses) over the first two years of life show promise in promoting child health and family functioning, and ameliorating disadvantage ('sustained nurse home visiting' or SNHV). When supported by SNHV, trials (predominantly overseas) have shown that families with risk factors for adverse child outcomes have higher immunisation rates [4], significantly improved quality of the home environment [5], parent-child interaction [6], child development [7], family functioning [4]; and reductions in the numbers of subsequent pregnancies [8,9], use of welfare [8], child abuse and neglect, and criminal behaviour [9].

There have been only two published Australian trials of SNHV [10,11]. Both trials commenced intervention postnatally and visited for up to six months. Systematic reviews have shown, however, that SNHV interventions that commence antenatally and visit for longer periods have greater success [5,12]. The effectiveness of a program of SNHV commencing antenatally and longer-term (2 years) intervention for at-risk mothers in the Australian context is, thus, unknown.

This trial aimed to determine the impact of a comprehensive SNHV program initiated antenatally for at-risk mothers who reside in a community characterised by profound socioeconomic disadvantage on outcomes including household environment and health, development and well-being of the family, mother and child. The trial was conducted in an area of disadvantage in South Western Sydney (SWS). Using the Australian Bureau of Statistics Standardised Index of Relative Disadvantage (now known as the Index of Relative Socio-economic Disadvantage) [13], this area (Postcode 2168) is in the lowest decile in Australia.

Australian governments (federal and state) are committed to a national agenda for early childhood, with a strong focus on development and use of Australian-relevant evidence, an outcomes focus, a focus on vulnerable communities, families and children, and strengths-based approaches. The Commonwealth has noted that 'much of the existing evidence base has been developed overseas, with limited Australian data on what works here' [14]. The Miller Early Childhood Sustained Home-visiting (MECSH) trial is a critical step in the development of an Australian evidence base and best practice models for SNHV; a key strategy for the delivery of services to promote the health and development of young Australians.

## Methods and design

The overarching hypothesis of the trial was that children born to at-risk mothers receiving SNHV will have significantly better environmental, child, maternal and family outcomes than those receiving usual care.

### Study Design

A randomised controlled trial design was undertaken. Eligible mothers were those living in the 2168 postcode area of Sydney, New South Wales (NSW) and identified as at-risk through the responses given by the expectant mother at the standardised psychosocial assessment [15] conducted by antenatal clinic midwives for all mothers booking into a large teaching hospital in South Western Sydney for confinement. Women were classified as at-risk when seen in the hospital antenatal clinic if they had any one of a number of factors present that have been shown to be risk factors for poorer coping as a parent [15]. These were:

1) A positive response to any of 12 psychosocial questions routinely asked in the antenatal clinic. These questions assess expected lack of practical and emotional support, stressors in the past 12 months, personality, mental health, history of abuse in the mother's childhood, and family violence (see Matthey et al. [15], for details of these questions and responses deemed to indicate 'at-risk' status). In addition, the presence of any one of the following also meant the woman was classified as 'at-risk': maternal age under 19 years, late antenatal care after 20 weeks gestation, and current substance misuse.

2) Current probable distress. This was assessed using the Edinburgh Depression Scale (EDS) [16]. An EDS score of 10 or more may approximate the subgroups labelled in other trials as 'psychologically vulnerable' or 'low psychological resources' [17]. This score was used by the hospital's antenatal clinic to be inclusive of all women with probable distress and is lower than the validated antenatal score of 13 or more (for minor depression) or 15 or more (for major depression) [15,18,19]. There is an increasing body of evidence from both animal and human studies that psychosocial distress in pregnancy has significant impacts on developmental and behavioural outcomes for children [20], and health in later life [21].

Mothers who required the use of an interpreter or who did not have a phone were ineligible to participate.

### Recruitment

Promotional material was made available through the administration services at the time of booking into the hospital for confinement and posters were displayed in the hospital antenatal clinic waiting room. Eligible participants were identified by the Senior Research Officer (SRO) who was provided daily with the records of all new bookings. Details of eligible women were entered onto a database, and were crosschecked with antenatal clinic staff at a weekly meeting to ensure that processes of recruitment to the trial did not adversely affect clinical referral processes for at-risk women. Once cleared for contact regarding the trial, the Research Assistant (RA) made the initial approach by telephone to potential participants, provided brief information and sought permission to visit the pregnant woman at home. Informed consent was not sought at this point.

The RA subsequently visited women who had given verbal permission in their homes, provided detailed information about the study, including the advice that they may or may not receive a home visiting intervention, and obtained the women's informed written consent. Once consent was obtained, the RA administered the antenatal baseline questionnaire. After baseline measures were completed, women were given a sealed envelope that contained information advising them of their group assignment. Once consent forms and baseline data were returned to the SRO, the intervention team was advised of the names and contact details of consenting women randomised to receive the MECSH intervention. Consenting mothers allocated to the comparison group and those who did not consent to participate were reassured that they would receive usual care.

One month after the children were born, and at 6, 12, 18, and 24 months postpartum, all participants were re-contacted by the RA. At each point verbal consent was obtained to visit the mother at home, to administer questionnaires and conduct observations. Records were kept of acceptance and attrition rates to allow later 'intention to treat' analyses.

### Data collection

Processes, impacts and outcomes were measured identically in both groups. The measures were consistent with the state-wide Families NSW (previously Families First) Outcomes Evaluation Framework [22]. Wherever possible, instruments had demonstrated validity and reliability and were chosen from those used in previous studies of home visiting or the NSW Health Child Health Survey [23]. Basic demographic data such as maternal age, country of birth, marital status, and parity were collected from the routine standardised hospital and community health data collections. The risk factors used to identify eligibility for the trial were recorded from the hospital obstetric database. These data were used to describe the sample. The number of home visits, early childhood health clinic visits and telephone consultations with early childhood nursing services, and the use of medical, other health, parental support and child care services was recorded from the routine community child health data collection and parental report. At each contact the occurrence of any of the following events was noted: maternal death, child death, child placement in out-of-home care. Impact and outcome measures are detailed in Figure 1.

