**Figure 1 F1:**
[figure not shown]
**Measurements**.

Study measures were obtained by interviewer administered questionnaire antenatally and at 1, 12, and 24 months postpartum. In addition, women were telephoned at 6 months postpartum to maintain contact and encourage study retention. Antenatal, 12 month and 24 month questionnaires were administered by face-to-face interview and included observation measures. Interviewer administration was chosen due to low literacy rates within the study population. At approximately 18 and 30 months standardised developmental assessments and observation of parent-child interaction were conducted and videotaped either at the hospital, community health facility or the family home. All questionnaires and standardised testing were administered in English.

With consent, hospital clinical and community service use data were obtained for the mother and her child from the hospital inpatient and outpatient records and community health records for the period from birth up to 24 months postpartum. These data are available for the whole sample and is not dependent on participant retention.

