### Statistical analyses

All data analysis will be carried out according to a pre-established analysis plan. The primary analysis will be intention-to-treat. Two sided significance tests will be used. Power calculations will be conducted on all parametric analyses. Only findings with power > 80%, CI = 95% and ά < 0.05 will be determined to be statistically significant. Differences between the intervention and comparison groups in the proportion of mothers using nursing, medical, other health, parental support and child care services will be analysed using contingency tables. Descriptive analyses will be undertaken of critical events such as death or child removal as the incidence of these events is low in the Australian population. Impact and outcome data collected at multiple time points will allow imputation of missing data for participants who did not complete every data point using appropriate techniques [24,25]. Child development and parent-child interaction measures, and quality of the home environment (HOME inventory) will be analysed cross-sectionally at each collection point. All other impact and outcomes measures will be analysed cross-sectionally at 1, 12 and 24 months, to estimate the prevalence of each impact and outcome, their association with demographic and risk factors, and differences between the intervention and comparison groups using contingency tables for non-parametric data and t-tests for parametric data. Longitudinal analyses will then be undertaken to compare differences in outcomes over time between the intervention and comparison groups using Repeated Measures ANOVA for parametric data and Friedmans two-way ANOVA for non-parametric data.

A priori subgroup analyses will be conducted using General Linear Modelling to assess differences between the intervention and comparison groups in impact and outcomes for: first-time mothers compared with mothers with two or more children; Australian born mothers compared with mothers born overseas; mothers with only one risk factor compared with mothers with multiple risks at the time of recruitment antenatally; and mothers with lower psychosocial resources due to probable distress at the time of recruitment (EDS score of 10 or more) compared with mothers with higher psychosocial resources for parenting (EDS score of 9 or less).

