### Retention and Participation

Figure 2 details the flow of participants in the study, including retention and participation at each follow-up point. Non-participation of study participants at each data point and loss to follow-up were primarily due to being unable to contact the women for data collection. Attempts were made to contact all 208 participating women at every data point. A participant was determined to be lost to follow-up when they missed two sequential contact points and were not subsequently recontacted at any later data points.

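### Study contact is the only source named for deaths and out-of-home placement, so these counts risk under-ascertainment although whole-sample health records are already held

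*Protocol article*

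**What the plan says.** The Data collection section gives a source for each kind of item. Demographics come from routine hospital and community health collections, eligibility risk factors from the hospital's obstetric database, and service use from the routine community child health collection plus what parents report. For the critical events it says: "At each contact the occurrence of any of the following events was noted: maternal death, child death, child placement in out-of-home care". It gives no record source for them.

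After Figure 1, the same section describes a source that does not depend on reaching the mother. It says that "hospital clinical and community service use data were obtained for the mother and her child"; the sources are hospital and community health files, and the period is birth to 24 months. On coverage it adds: "These data are available for the whole sample and is not dependent on participant retention".

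On contact, the Recruitment section says: "One month after the children were born, and at 6, 12, 18, and 24 months postpartum, all participants were re-contacted by the RA", with verbal consent sought each time. The Retention and Participation section says that contact was attempted with all 208 women at every data point, and that non-participation and "loss to follow-up were primarily due to being unable to contact the women for data collection". A woman counted as lost after two consecutive missed points with no later recontact. The Abstract gives active follow-up of 86%, 74% and 63% at 12, 24 and 30 months; the Discussion gives the last as 62.5%.

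The Statistical analyses section plans description only: "Descriptive analyses will be undertaken of critical events such as death or child removal as the incidence of these events is low".

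**The concern.** Under the stated rule, an event is detected by reaching the mother, and the event can stop that from happening. A mother who has died cannot be interviewed. A mother whose child has died or been removed may plausibly decline a visit about that child. Either could be filed as loss to follow-up, with the event never counted.

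Because only description is planned, the counts and their denominators are the whole result for these events. With events this rare, missing one or two changes the picture. A source that could find some of the missing events is already held for every participant, but the article does not say that it serves this purpose.

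**Working it through.** **Inputs from the article**
- Randomised: 111 + 97 = 208 (Sample Description).
- Active follow-up: 86%, 74% and 62.5% at 12, 24 and 30 months (Abstract, Discussion).
- Event counts, event rates, or contact probability after an event: none given.

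**Step 1: the article's own figure.** 130/208 = 62.5%, which agrees with the Abstract's 63%. At 24 months, 0.74 × 208 = 153.9, so about 154 women were in active follow-up and about 54 were not.

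**Step 2: formulas.** Let p be the true risk, c0 the probability of contact without an event, and c1 = r × c0 the probability of contact after one. With no other source:
- events recorded = 208 × p × c1
- count over all 208, relative to the truth = c1
- rate among contacted women = p × c1 / (p × c1 + (1 − p) × c0)

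**Step 3: events do not affect contact (r = 1).** The count over all 208 is low by 1 − c0:
- 12 months: 1 − 0.86 = 14%
- 24 months: 1 − 0.74 = 26%
- 30 months: 1 − 0.625 = 37.5%

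The rate among contacted women is unbiased in this case, so the choice of denominator matters.

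**Step 4: events reduce contact (r < 1).** Take c0 = 0.74 and, as an illustration, p = 3%, or 208 × 0.03 = 6.24 true events. Both p and r are assumptions.

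| r | c1 | Events recorded | Shortfall over all 208 | Rate among contacted |
|---|---|---|---|---|
| 1 | 0.74 | 4.62 | 26% | 3.00% |
| 0.75 | 0.555 | 3.46 | 44.5% | 2.27% |
| 0.5 | 0.37 | 2.31 | 63% | 1.52% |
| 0.25 | 0.185 | 1.15 | 81.5% | 0.77% |

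The shortfall column does not depend on p. Once r is below 1, the rate among contacted women is low too, at roughly r times the truth.

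**Step 5: how far 74% can be trusted as contact.** Treating everyone out of active follow-up at 24 months as never observed overstates the loss, because their earlier contacts count. In the other direction, the Figure 2 legend counts a woman as active if she completed the previous data point, so an event after that visit could still be missed. Any event found in the whole-sample records reduces the shortfall. The 26% indicates scale; it is not an estimate.

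**The case against.** The strongest reply is that the article never says contact was the sole source. It is a condensed account, Figure 1 is not shown, and nothing states that the whole-sample records were left unused for these events. Contact was also cumulative and attempted with all 208 women at every point, so an event missed once could surface later, and a failed attempt can itself reveal a death or placement. The attrition findings show no simple gradient with risk. The Discussion reports equal retention for women with multiple risks, domestic violence or substance use, and better retention for those abused as children. Late bookers and women without full-time employment income were retained less well, but that is not evidence about these events. Finally, the events are only described, and no test or power claim rests on them.

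Most of this stands, and it limits the claim to a risk of unknown size. It does not remove the point. The section states a rule for these events beside record sources for other items, so the criticism is of what is written and not of a detail left elsewhere. Repeated attempts help only where a later attempt succeeds, and the main reason for loss was that attempts failed.

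**Conclusion.** The point holds as a risk of under-ascertainment. Contact is the only source named for the three events, contact was incomplete, and the events can prevent it. If events do not affect contact and no other source is used, a count over all 208 is up to about 26% low, taking 74% active follow-up as contact. It is lower still if events reduce contact, but the article gives no figure for that. The matter is worth correcting; it does not touch the trial's tested comparisons.

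A reader might infer four stronger things that the article does not support:
- **That the rates are shown to be biased downwards.** No event data are reported, and the rate among contacted women is biased only if events change the chance of contact.
- **That the records were not used.** The text is silent on this.
- **That 24-month participation (51.4%) is the share reached.** This treats one missed visit as no information over the whole study, so no shortfall should be based on it.
- **That the arms were watched unequally because intervention families saw programme staff.** The Data collection section says measurement was identical in both groups, and nothing describes programme staff reporting events to the research team. The comparison group's lower participation is reported as not significant. A difference by arm is speculation.

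**What to change.** Ascertain maternal death, child death and out-of-home placement for all 208 mother-child pairs, by the same rule in both arms. Use the hospital and community health records already obtained from birth to 24 months as the first source and study contacts as the second. For each arm, report the number of events, the number with known status and the number with unknown status, so that the denominator is explicit.

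The cost is a little extra extraction, with no new visits. The records have limits: they may miss placements and deaths outside hospital, and they stop at 24 months, so anything later still depends on contact. The unknown-status count makes those limits visible.

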**Figure 1 F1:**
[figure not shown]
**Measurements**.

Study measures were obtained by interviewer administered questionnaire antenatally and at 1, 12, and 24 months postpartum. In addition, women were telephoned at 6 months postpartum to maintain contact and encourage study retention. Antenatal, 12 month and 24 month questionnaires were administered by face-to-face interview and included observation measures. Interviewer administration was chosen due to low literacy rates within the study population. At approximately 18 and 30 months standardised developmental assessments and observation of parent-child interaction were conducted and videotaped either at the hospital, community health facility or the family home. All questionnaires and standardised testing were administered in English.

With consent, hospital clinical and community service use data were obtained for the mother and her child from the hospital inpatient and outpatient records and community health records for the period from birth up to 24 months postpartum. These data are available for the whole sample and is not dependent on participant retention.

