### Sample size

Funding allowed three nurses to be employed to deliver the intervention, each with a maximum caseload of 25 mothers (in accordance with NSW Department of Health guidelines). Hence, 75 families could be receiving intervention at any one time. Previous randomised controlled trials reported in the literature have had a median number of subjects of 65 per group (range 9–347). A sample size of 75 subjects per group has power of 0.80 at the 95% level to detect effect sizes of 0.5 or larger for the HOME Inventory, Bayley Scale of Mental Development and maternal health (SF-12), and detect differences of less than 22% in the rates of immunisation, child injury and breast-feeding. In systematic reviews of home visiting conducted by Elkan [12] and MacLeod [5] effects of at least these sizes were found in the HOME Inventory; a meta-analysis of trials using the Bayley Scales of Mental and Motor Development showed an overall effect size of 0.17, however, effect sizes were larger (up to 0.5 for mental development and 0.4 for motor development) in studies that assessed development at 12 months or later; the pooled odds ratio for immunisation and breastfeeding at 3 months were 1.40 and 1.34 respectively; the pooled odds ratio for reduction in child injury in studies aimed at improving a range of child and maternal health outcomes was 0.76; significant change in depression and stress scores were reported in studies using EDS and the Parenting Stress Index. Trials with fewer than 50 subjects have shown significant intervention effects in the quality of the home environment measured using the HOME inventory, child mental development measured using the Bayley Scale of Infant Mental Development, immunisation rates, possible maternal depression measured using the EDS, parenting stress measured using the Abidin Parenting Stress Index, and transition to solids [12]. Recruitment took place over the period February 2003 to March 2005. This allowed a planned recruitment of 90 subjects per group whilst maintaining the maximum intervention caseload of 75, to allow for a proposed 15% loss to follow-up.

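### No breast-feeding comparison is stated between 1 and 12 months, and two sections disagree on whether any questionnaire was given at 6 months

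*Protocol article*

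**What the plan says.** - **Power statement (Protocol article, Sample size).** With 75 women per group the trial is said to "detect differences of less than 22% in the rates of immunisation, child injury and breast-feeding". No base rate or time point is attached. The prior evidence cited is that "the pooled odds ratio for immunisation and breastfeeding at 3 months were 1.40 and 1.34 respectively".
- **Analysis (Statistical analyses).** Child development, parent-child interaction and the HOME inventory are handled separately. For the rest: "All other impact and outcomes measures will be analysed cross-sectionally at 1, 12 and 24 months, to estimate the prevalence". Categorical data go to contingency tables and parametric data to t-tests. Longitudinal analyses follow, but no further time points are named.
- **Contacts, first account (Recruitment).** "One month after the children were born, and at 6, 12, 18, and 24 months postpartum, all participants were re-contacted by the RA". The next sentence says that at each of these points consent was taken for a home visit with questionnaires and observations.
- **Contacts, second account (Data collection, text below the Figure 1 caption).** Questionnaires were given antenatally and at 1, 12 and 24 months. At 6 months, "women were telephoned at 6 months postpartum to maintain contact and encourage study retention".
- **Measures.** Data collection refers the reader to Figure 1 for the impact and outcome measures; that figure is not shown.

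**The concern.** Stopping breast-feeding is an event in time. A prevalence at 1 month sees it early, and a prevalence at 12 or 24 months may see it after many women have stopped. How many is an assumption, since the article gives no weaning data. If the programme lengthens breast-feeding within the first year, much of the difference could fall between the first two snapshots and be reported as no difference. The result could also not be set against the 3-month effect that the article itself cites.

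The gap overlaps a busy part of the programme. On the minimum schedule in the Intervention section, postnatal visits number about 6 in the first 6 weeks, 3 more to 12 weeks, 3 more to 6 months and 9 more to 2 years. That is about 12 of 21 in the first 6 months, of which about 8 come after month 1. Infant nutrition is part of the visit content.

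The conflict over the 6-month contact matters because it decides whether feeding data exist inside the gap.

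**Working it through.** **1. The time points side by side.**

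| Section | 1 month | 6 months | 12 months | 24 months |
|---|---|---|---|---|
| Recruitment | visit, questionnaires | visit, questionnaires | visit, questionnaires | visit, questionnaires |
| Data collection | questionnaire | retention call | questionnaire | questionnaire |
| Statistical analyses (breast-feeding) | compared | not mentioned | compared | compared |

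The first two rows contradict each other at 6 months. The third row leaves 1 to 12 months empty whichever of them is true. Data collection adds that deaths and out-of-home placement were noted at every contact, so something was recorded at 6 months on either account. Whether feeding was recorded is not stated.

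**2. The plan's own figure.** Inputs are 75 per group and power 0.80 (Sample size), two-sided 5% tests ("Two sided significance tests will be used") and a 22-point difference. The base rate is not given; take 50% against 72%, mean 61%.

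- SE under no difference = √(2 × 0.61 × 0.39 / 75) = 0.0796
- SE under the difference = √((0.50 × 0.50 + 0.72 × 0.28) / 75) = 0.0776
- Power = Φ((0.22 − 1.96 × 0.0796) / 0.0776) = Φ(0.82) = 0.795

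The figure reproduces (76 per group would be needed for 0.80). At 75 per group the detectable difference runs from 15.0 points at an assumed lower rate of 5% to 22.7 points at 40%. It is not derived from the cited odds ratio: 1.34 on a 50% base gives odds of 1.34 and a rate of 1.34/2.34 = 57.3%, a difference of 7.3 points. The 22-point figure needs no correction on account of timing.

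**3. What the gap could cost (illustration).** Assumptions not in the article: exponential weaning, S(t) = 2^(−t/median); known stopping times to 12 months; 75 per arm.

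Medians of 3 and 5 months:

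- Month 1: 0.794 against 0.871, difference 0.077, pooled SE 0.0610, z = 1.26, power Φ(1.26 − 1.96) = 0.24
- Month 12: 0.0625 against 0.1895, difference 0.127, pooled SE 0.0542, z = 2.34, power 0.65
- Month 24: 0.004 against 0.036, z = 1.40, power 0.29
- Log-rank to 12 months: events = 75 × 0.9375 + 75 × 0.8105 = 131; hazard ratio 3/5 = 0.60; z = √(131/4) × 0.511 = 2.92; power 0.83

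The same formulas with other medians:

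| Medians (months) | 1 month | 12 months | 24 months | Log-rank to 12 months |
|---|---|---|---|---|
| 2 and 3 | 0.23 | 0.32 | 0.07 | 0.68 |
| 3 and 5 | 0.24 | 0.65 | 0.29 | 0.83 |
| 4 and 6 | 0.14 | 0.50 | 0.32 | 0.61 |
| 6 and 9 | 0.11 | 0.49 | 0.46 | 0.53 |

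The log-rank test exceeds each single snapshot in all four rows, but in the last row only slightly.

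**The case against.** The strongest reply is that the measure is not visible. Figure 1 may contain a recalled duration of breast-feeding asked at 12 months. A t-test on duration would fit the stated methods and would cover months 1 to 12. The article also refers to a pre-established analysis plan, which may already settle this. That stands, and it is why the gap is conditional. It does not remove the point: the words used for this outcome are rates and prevalence, and a t-test on duration has no good way to treat women still feeding at interview or lost before it.

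The illustration is also open to challenge. The medians are invented, exponential weaning gives proportional hazards (the best case for log-rank), and the comparison is with single snapshots rather than the longitudinal analyses. Full data on 75 per arm is optimistic, since the Discussion reports participation from 67.7% at 1 month down to 51.4% at 24 months. All of this stands; the figures show direction only.

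The 1-month comparison is not empty either. It follows all the antenatal home visits and about four postnatal ones.

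A reader might go further and infer four things that the article does not support:

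- **That the 6-month contact collected nothing.** Recruitment describes questionnaires there, and critical events were noted at every contact.
- **That the trial was sized on breast-feeding.** Nurse caseload (3 × 25 = 75) set the number, and breast-feeding is one of six outcomes in the power sentence.
- **That the plan relies on the 3-month effect.** It is cited as background and does not produce the 22 points.
- **That most weaning falls in the gap.** The article holds no data on this.

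**Conclusion.** The point holds in a limited form. As written, breast-feeding is compared only at 1, 12 and 24 months. Nothing between 1 and 12 months is compared, including the 3-month point of the cited effect, unless duration was recorded. Separately, Recruitment and Data collection contradict each other on the 6-month contact; this needs no outside assumption.

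The possible loss of power ranges from substantial (0.65 against 0.83 with medians of 3 and 5 months) to trivial (0.49 against 0.53 with 6 and 9), and rests wholly on assumed weaning curves. It concerns one secondary strand of a trial with many outcomes and does not touch the trial's validity. It is worth acting on because the analysis is still described in the future tense and the change is cheap.

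**What to change.** 1. Reconcile Recruitment and Data collection on the 6-month contact, and state which feeding data, if any, exist at that point.
2. State whether the breast-feeding measure is current status, duration or age at stopping.
3. Where stopping age or 6-month status was recorded, replace the 1-, 12- and 24-month prevalence comparison with time from birth to stopping breast-feeding. Use Kaplan-Meier curves with a log-rank test or Cox model, censored at last contact, or an interval-censored method if only status at contacts is known. Read the 3- and 6-month proportions from the curve.
4. If neither was recorded, keep the stated comparisons and say that the period from 1 to 12 months is untested.
5. Date the change before any comparison of the groups on this outcome.

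New questions in the 6-month contact are not an option: recruitment closed in March 2005 and 30-month retention is already reported. Community health records help only if they hold feeding data, which the article does not say.

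The cost is one standard analysis and a few sentences of clarification. The downside is recall error in stopping age, chiefly for women who reported it only at 12 months.
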